#### *Sample Size*

We hypothesize CDS will reduce incidence of HAVTE in those i) predicted at high risk by VTEAI and ii) without evidence of pharmacologic prophylaxis in half, from baseline 4.3% incidence (562/12,946 events) to 2.2% incidence, which will require 2,236 encounters. Sample size calculation indicates at least 1,118 patient encounters are needed in each arm to achieve 80% power with 5% probability of type I error. Using historical data from 2023-2024, we see encounter counts of 150-230 encounters per month meeting these criteria. We will therefore conduct the RCT for one (1) year to meet required sample size.

#### *Recruitment*

Because of the pragmatic nature of this RCT, enrollment/randomization occurs at the start of each encounter, when the VTE-AI risk score is calculated. No additional recruitment will be conducted.

---

#### *Post-Implementation Evaluation*

We will analyze the BPA utilization data routinely collected within the Epic EHR to identify providers who encountered the BPA in regular patient care. These data include logs of BPA views and actions taken as well as orders written via the BPA and linked order sets.

## **7.0 Risks**

This protocol presents minimal risks to participants. The risk model might identify risk in those not at high risk of HA-VTE, leading to pharmacologic prophylaxis that might not otherwise have been ordered. Adverse events include potential increased bleeding risk if prophylaxis is ordered from the CDS prompt that would not otherwise have been ordered. Bleeding from VTE prophylaxis in general is a rare event. The risk model is not perfect and might not identify risk in those who are at risk – it is not intended to preempt providers prophylaxing any patient (or all patients) for HA-VTE if they choose to do so.

## **8.0 Reporting of Adverse Events or Unanticipated Problems Involving Risk to Participants or Others**

### *Harms*

The PIs are responsible for monitoring study data, assuring protocol compliance, and conducting safety reviews. Because of the pragmatic nature of the study interventions (CDS decision aids), adverse events or other problems are anticipated to be rare. In the unlikely event that such events occur, unanticipated problems involving risks to subjects or others that are i) serious, ii) unanticipated, and iii) possibly or definitely related to research procedures will be reported immediately to the PI, and in writing within 7 days to the VUMC IRB. The PI will apprise fellow investigators and study personnel of such adverse events that occur during the conduct of this research project through regular study meetings. Continuing review reports will be submitted annually to the IRB summarizing study progress, adverse events, complaints about the research or withdrawals, and any protocol violations.

We will follow the VUMC Human Research Protections Program (VHRPP) guidelines that require investigators to promptly notify the IRB within 7 days of the occurrence when such unexpected Adverse Events (AEs) occur. These are events that could possibly be related to the intervention, or occur more frequently or are more severe than anticipated. VHRPP requires that any AE that is unexpected and related or possibly related to the research be reported. Adverse events not meeting this definition will be reported at the time of continuing review.

Unanticipated problems involving risks to subjects or others will be reported immediately, within twenty-four (24) hours of their discovery to the PI, and in writing within 7 days to the IRB. The PI will apprise fellow investigators and study personnel of all AEs that occur during the conduct of this research project through regular study meetings. Annual reports will be submitted by the study coordinator to the responsible IRBs summarizing study progress, AEs, complaints about the research, and any protocol violations.

### *Auditing*

Study data will be analyzed by the PI and study team every three months for 1) continued validity of VTE-AI to prognosticate HA-VTE; 2) proper functioning of the VTE-AI model [e.g., ensuring all predictors continue to be calculated appropriately for patients]; 3) rates of HA-VTE and bleeding events. Because this study necessitates close collaboration with providers receiving BPAs, the study team will have monthly small-group virtual meetings with providers in study sites at VUMC to assess for problems or perceived AEs related to the study protocol, though none are anticipated.

## **9.0 Study Withdrawal/Discontinuation**

Providers may dismiss the BPA and not act on its recommendations at any time. No other intervention is planned. Patients would be unaware of the providers'

decisions in that case unless the provider chooses independently to discuss the BPA with them.

## **10.0 Statistical Considerations**

The study team determined the following power analysis.

We hypothesize CDS will reduce incidence of HAVTE in those i) predicted at high risk by VTEAI and ii) without evidence of pharmacologic prophylaxis in half, from baseline 4.3% incidence (562/12,946 events) to 2.2% incidence, which will require 2,236 encounters. Sample size calculation indicates at least 1,118 patient encounters are needed in each arm to achieve 80% power with 5% probability of type I error. Using historical data from 2023-2024, we see encounter counts of 150-230 encounters per month meeting these criteria. We will therefore conduct the RCT for one (1) year to meet required sample size.

---

## **11.0 Privacy/Confidentiality Issues**

All study experiments occur solely in the context of already-scheduled clinical care and among patients and providers already intending to interact for purposes of healthcare delivery. No data outside that patient's health record are used in the calculation of VTE-AI or in study conduct. Because these interactions occur solely in routine healthcare encounters, the same confidentiality rules apply as in standard of care.

Study data are secured on servers in the VUMC data center or in VUMC Health Information Technology production systems only. These systems are secured via personal, physical, and technical controls including their invisibility to networks outside the VUMC firewall. User credentials are maintained by the VUMC Active Directory and Information Technology and are necessary to access any study data. Only those credentialed and on an approved IRB will have permissions to access study data on these servers. No paper records will be generated nor recorded in this study. All data collection will be digital and will leverage operational clinical systems and EHRs in their generation. No new data collection mechanisms will be required and therefore no new vulnerabilities generated.

## **12.0 Follow-up and Record Retention**

The study will last six months.

As per IRB policy VI.B, all study data will be maintained for six (6) years from the date of the last use of study Protected Health Information (PHI) - at the conclusion of the trial period to identify patients in need of outcome data collection (which is based in EHR queries only).

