## **5.0 Enrollment/Randomization**

Randomization will be done in the Epic EHR, built-in functionality. One half will be randomized to VTE-AI-driven CDS and one-half to standard of care.

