#### *Participant Timeline*

Randomization, interventions, and assessments all occur within each study encounter with no follow-up or additional interventions for either study participants (practitioners) or patients.

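### Section 12.0 gives a six-month study and the sample-size text a one-year RCT; six months cannot reach 2,236 encounters at any flow the protocol reports

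*Protocol*

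**What the plan says.** The protocol (version 4) gives two lengths for the trial.

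- Section 12.0, Follow-up and Record Retention: "The study will last six months". No reasoning accompanies it.
- Section 6.0, Sample Size, repeated in Section 10.0, Statistical Considerations: "We will therefore conduct the RCT for one (1) year to meet required sample size". This is presented as a consequence of the target and the flow. The target is 4.3% falling to 2.2%, for which "at least 1,118 patient encounters are needed in each arm to achieve 80% power with 5% probability of type I error", or 2,236 in total. The flow is given as "Using historical data from 2023-2024, we see encounter counts of 150-230 encounters per month meeting these criteria".

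Two other statements bear on how the six months can be read. Under Participant Timeline (Section 6.0), everything takes place inside the encounter, "with no follow-up or additional interventions for either study participants (practitioners) or patients". Section 5.0 sets equal allocation: "One half will be randomized to VTE-AI-driven CDS and one-half to standard of care".

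**The concern.** All of these are operative statements in the current version; none belongs to a log of superseded text. A total study length cannot be shorter than the RCT it contains, so they cannot all be right.

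The conflict matters because enrolment is automatic in the EHR. There is no recruitment effort to adjust, so the closing date in effect sets the sample size. A trial closed at six months under Section 12.0 would fall well short of the size on which the stated power rests, and a null result could not be taken as evidence against the hypothesised halving. In addition, the Auditing text in Section 8.0 has the team look at HA-VTE rates every three months. With two durations on paper, a stop at either date could be defended from the text after those rates had been seen.

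**Working it through.** **Inputs (all from the protocol unless marked)**

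- Event rates: p1 = 0.043 and p2 = 0.022 (Section 10.0).
- Size: 1,118 per arm, 2,236 in total, 80% power, 5% type I error (Section 10.0).
- Flow: 150 to 230 eligible encounters per month (Section 10.0); midpoint 190.
- Allocation 1:1 (Section 5.0).
- Assumptions: two-sided test (sidedness is not stated, but this choice reproduces the plan's figure) and no loss (no inflation is stated).

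**Step 1. Reproduce the plan's sample size.** Pooled-variance formula without continuity correction, with p̄ = 0.0325:

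n per arm = [1.960·√(2p̄(1−p̄)) + 0.8416·√(p1(1−p1) + p2(1−p2))]² / (p1−p2)²

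= [1.960 × 0.25077 + 0.8416 × 0.25033]² / 0.021² = 0.49308 / 0.000441 = 1,118.09.

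This matches the stated 1,118. A one-sided test gives 881, and a two-sided test with continuity correction gives 1,212; neither matches.

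**Step 2. Accrual and power for each stated duration.** Encounters N = months × flow, n = N/2 per arm, and

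power = Φ{[(p1−p2)√n − 1.960·√(2p̄(1−p̄))] / √(p1(1−p1) + p2(1−p2))}

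Example, six months at 150: n = 450, (0.021 × 21.213 − 0.49151) / 0.25033 = −0.184, so Φ = 0.427.

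| Duration | Flow per month | Encounters | Share of 2,236 | Power |
|---|---|---|---|---|
| 6 months | 150 | 900 | 40% | 43% |
| 6 months | 190 | 1,140 | 51% | 52% |
| 6 months | 230 | 1,380 | 62% | 59% |
| 12 months | 150 | 1,800 | 81% | 71% |
| 12 months | 190 | 2,280 | 102% | 81% |
| 12 months | 230 | 2,760 | 123% | 88% |

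**Step 3. Flow needed.**

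- Six months: 2,236 / 6 = 372.7 per month, which is 372.7 / 230 = 1.6 times the top of the stated range. The smallest shortfall is 2,236 − 1,380 = 856.
- Twelve months: 2,236 / 12 = 186.3 per month on average, which lies inside the stated range and just below its midpoint.

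**Step 4. Sensitivity.** With exact halving (2.15% in place of 2.2%), six-month power is about 45% to 62%. With a continuity correction at 4.3% versus 2.2%, it is about 35% to 54%. The conclusion does not change.

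**The case against.** Three arguments can be made for the protocol.

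**The six months may mean something else.** The sentence stands under a heading about follow-up and retention, so it might describe a phase after accrual. The Participant Timeline excludes such a phase, and the 30-day readmission outcome would account for only about one month. This reading does not stand.

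**It may be leftover text.** The one-year statement appears twice and is derived from the flow, while the six-month sentence stands alone without a reason. This is plausible, and it means that closure at six months is a possibility the text permits, not a demonstrated plan. It explains the conflict but does not remove it.

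**The one-year plan is sound.** A reader might infer from the table that one year also fails to secure 80% power, because the low end falls 436 encounters short. The protocol does not support that as an error. The range reads most naturally as month-to-month spread, so 1,800 and 2,760 require the whole year to average at one extreme. The 186.3 figure is a 12-month average, and single months may fall below it. As an illustration, assume independent months spread uniformly over 150 to 230. The monthly SD is 80/√12 = 23.1 and the 12-month SD is 23.1 × √12 = 80. The yearly total is then about 2,280 ± 1.96 × 80, or 2,123 to 2,437, with power near 78% at the lower bound. Correlated months or a shift since 2023-2024 would widen this, but the protocol shows neither. The one-year margin is thin (2% at the midpoint), which calls for caution and is not a mistake. A fixed calendar window is also a legitimate choice for an EHR-embedded pragmatic trial, so closure by count is not required.

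**Conclusion.** The contradiction is real and needs correcting. At every flow the protocol reports, the six-month duration cannot deliver the stated size: it gives 40% to 62% of 2,236 encounters and about 43% to 59% power against the stated 80%. These powers assume 4.3% versus 2.2%, a two-sided 5% test, equal arms, no loss, and a flow during the trial like that of 2023-2024.

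The point goes no further than that. The sample-size calculation itself is correct. It would be too strong to say that six months halves the power: 43% is 53% of the stated 80%, but that is the low end, and 59% at the high end is 74% of it. The one-year period agrees with the protocol's own figures at the midpoint flow.

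**What to change.** **Required.** Replace the six-month sentence in Section 12.0 with a cross-reference to the one-year RCT period in Section 6.0 (Sample Size) and Section 10.0, so that a single duration governs. The cost is a one-sentence protocol amendment, with no change to design, conduct or sample size.

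**Optional.** Because the one-year margin is thin, the sample-size text could add either of the following:

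- a statement that one year meets 2,236 if flow averages at least about 186 per month, and that power would be about 71% if it averaged 150 (1,800 encounters); or
- a provision to extend the period until 2,236 encounters that are high-risk by VTE-AI and without pharmacologic prophylaxis have been randomised. The population must be named, because the eligibility text admits all inpatients. At 150 per month this takes 2,236 / 150 = 14.9 months, about three months more of an alert already in place.

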## **13.0 Ethics and Dissemination**

*Institutional Review Board/Ethics Review Board Approval*

Protocol Version #: 4

Protocol date last updated: 7/11/2025

VUMC IRB #241978

VUMC IRB Approval pending.

*Protocol Amendments*

Changes to trial protocols including eligibility criteria, outcomes, or analyses will be communicated to the governing IRB, updated in national registration (ClinicalTrials.gov), clinical trial site leadership and participating clinicians within one calendar day.

*Waiver of Consent – in-clinic preventive CDS*

Waiver of consent will be pursued for the clinical intervention CDS. This study aims to measure the effectiveness of a risk model-driven BPA on provider behavior. Multiple factors contribute to impracticability to obtain consent. Consenting only those identified at highest risk would itself introduce selection bias and might alter behavior of staff/providers aware that consent had taken place in a manner that would alter study results. Informed consent at the start of the visit disrupts that intended workflow and might bias decision-making. Waiver prevents that issue from i) disrupting care for those patients and ii) unduly affecting the study itself.

*Waiver of Consent – minimal risk*

This study does not involve an investigational intervention given or administered directly to patients. This study poses no greater than minimal risk to study participants. VUMC has become a leader in pragmatic, minimal risk clinical trial designs like this one and we have engaged the Learning Health System for high-level guidance in study design. Our study team benefits greatly from the experiences and expertise of our colleagues who have completed similar studies under waiver of informed consent. The potential benefit of this study would come through better provision of screening to those at risk who would not otherwise be screened in current state. Waiver of consent will have no impact on privacy for patients or providers because the CDS will be applied only in routine encounters already scheduled for unrelated reasons, and no data from this study exist outside the bounds of the individuals' EHRs.

*Confidentiality*

Data will be collected from the EHR and stored securely in the VUMC Data Center on servers owned by the study team for later analysis. These systems are designed to securely store Protected Health Information and include encrypted storage, multifactor authentication, and both physical (locked doors, secure facility) and technical (active directory user authentication) controls. Protected Health Information, while necessary to conduct study analyses, will never be exported from these servers or shared.

Data to be collected to calculate VTE-AI include type of admission; heart rate; diagnostic codes (for clinical comorbidities); central line placement data; laboratory data including basic metabolic panel and c-reactive protein.

Protocol Version #: 4

Protocol date last updated: 7/11/2025

VUMC IRB #241978

*Declaration of Interests*

No conflicts of interest exist, financial or otherwise, for any members of the study team relevant to this research.

*Access to data*

Two study team members have access to raw EHR data needed to conduct study analyses: [name] (PI), [name] (developer/analyst). Only members of HealthIT with Physician Builder credentials necessary to design and implement the trial CDS might access EHR data within our vendor EHR: e.g., [name] (HealthIT).

*Ancillary and Post-trial care*

Not applicable to this study.

*Dissemination Policy*

Our team will disseminate trial findings through peer-reviewed journals and national conferences including biomedical informatics, internal medicine, and hematology. Where possible, the team will preprint our manuscripts at the start of peer review for more transparent dissemination of our results. We will pursue open access publication where available to maximize dissemination.

No professional writers will be employed in dissemination.

Because of the sensitive nature of the PHI needed to conduct this trial, public access to participant-level data will not be possible. Statistical code and the full protocol for the study (this document) will be disseminated with peer-reviewed publication as appropriate.

**14.0 Appendices**

*Informed consent materials*

Waiver of consent, as above

*Biological Specimens*

Not applicable
